## Appendix 5: Modified Visual RECIST

### Modified Visual RECIST Quick Reference:

#### Eligibility

- Only patients with measurable NMSC lesions at baseline should be included

**Measurable disease** - the presence of at least one measurable lesion and its neoplastic nature should be confirmed by histology.

**Measurable lesions** - lesions that can be accurately measured in at least one dimension with longest diameter  $\geq 5$  mm with the naked eye.

- All measurements should be taken and recorded in metric notation, using a ruler or callipers. All baseline evaluations should be performed as closely as possible to the beginning of treatment and never more than 4 weeks before the beginning of the treatment.
- The same method of assessment and the same technique should be used to characterize each identified and reported lesion at baseline and during follow-up.
- Clinical lesions will only be considered measurable when they are superficial (e.g., skin nodules and palpable lymph nodes). For the case of skin lesions, documentation by colour photography, including a ruler to estimate the size of the lesion, is recommended.

#### Methods of Measurement

- Visually assess the lesion(s) to measure target lesions selected for response assessment.
- Lesions on contoured surfaces such as the ear are acceptable as measurable lesions.
- Confirm the complete disappearance of lesions assessed by clinical examination.
- The utilization of Dermascopy is permissible as required and should be included as part of the 6 month follow up visit.
- Tumour histology alone cannot be used to assess response. If Histology is taken at the 12-month mark, then this histology must be negative in addition to CR visually, for a patient to be considered in complete response.
- Histology can be used to differentiate between PR and CR at the 12-month mark if tumour is visible, suspected or is site clinical practice to do so.

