#### **12 month follow up visit:**

- Photography of treated lesions (medical photographer or site digital camera)
- CTCAE grading
- Quality of Life questionnaire completed via trial App (or on paper during the visit if subject does not have a smart phone)
- Cosmetic outcome; subject rated. To be completed on Trial app (or directly into the eCRF if the subject does not have a smart phone). VAS image found in the protocol appendix 3
- Cosmetic outcome: Clinician rated. To be completed into the eCRF using VAS in the protocol appendix 3
- Modified Visual RECIST assessment. Guide to assessment is found in protocol appendix 5
- Histology to be performed if lesion is visible, suspected or if this is the site's regular clinical practice

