**24 month follow up visit:**

- Photography of treated lesions (medical photographer or site digital camera)
  - CTCAE grading. Grading can be found in protocol appendix 1
  - Cosmetic outcome; subject rated. To be completed on Trial app (or directly into the eCRF if subject does not have a smart phone). VAS image found in the protocol appendix 3
  - Cosmetic outcome: Clinician rated. To be completed into the eCRF using VAS in the protocol appendix 3
  - Modified Visual RECIST assessment. Guide to assessment is found in protocol appendix 5
- 
- Histology to be performed if lesion is visible, suspected or is the site's regular clinical practice
  - General review for wound complications and radiation changes. Radiation changes at months 24 are to be recorded as the CTCAE grading in protocol appendix 1, **excluding** Radiation dermatitis.

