### Response Criteria

#### Evaluation of target lesions

- \* Complete Response (CR): Disappearance of all target lesions
- \* Partial Response (PR): At least a 30% decrease in the sum of the LD of target lesions, taking as reference the baseline sum LD
- \* Progressive Disease (PD): At least a 20% increase in the sum of the LD of target lesions, taking as reference the smallest sum LD recorded since the treatment started or the appearance of one or more new lesions
- \* Stable Disease (SD): Neither sufficient shrinkage to qualify for PR nor sufficient increase to qualify for PD, taking as reference the smallest sum LD since the treatment started

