**Table 4. Evaluation of best overall response**

| Target lesions
At 12 months | New Lesions at
treated site(s) | Overall response
at 24 months |
|--------------------------------|-----------------------------------|----------------------------------|
| CR                             | No                                | CR                               |
| PR                             | No                                | PR                               |
| SD                             | No                                | SD                               |
| PD                             | Yes or No                         | PD                               |
| CR                             | Yes                               | PD                               |

PR

Yes

PD

CR: complete response; PR: partial response; SD: stable disease; PD: progressive disease

- In some circumstances it may be difficult to distinguish residual disease from normal tissue. When the evaluation of complete response depends on this determination, it is recommended that the residual lesion be investigated (biopsy/Histology) to confirm the complete response status.

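### Appendix 5 gives two incompatible rules for a lesion still visible at 12 months with a negative biopsy, so its complete-response status depends on which rule the site follows

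*Protocol*

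**What the plan says.** The response criteria in Appendix 5 define "Complete Response (CR): Disappearance of all target lesions". The synopsis (Efficacy) also defines CR as disappearance.

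Methods of Measurement in Appendix 5 then adds two bullets on histology:

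- Fifth bullet: "Tumour histology alone cannot be used to assess response". If histology is taken at 12 months, "this histology must be negative in addition to CR visually, for a patient to be considered in complete response".
- Sixth bullet: "Histology can be used to differentiate between PR and CR at the 12-month mark if tumour is visible, suspected", or where biopsy is the site's practice.

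A note under Table 4 concerns residual tissue that is hard to tell from normal tissue. For that situation "it is recommended that the residual lesion be investigated (biopsy/Histology) to confirm the complete response status".

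Biopsy is scheduled at two visits. Section 9.1.3 says for 12 months: "Histology to be performed if lesion is visible, suspected or if this is the site's regular clinical practice". The 24-month entry is nearly identical: "Histology to be performed if lesion is visible, suspected or is the site's regular clinical practice". Table 2 agrees and schedules no post-treatment histology at 6 months.

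Appendix 5 leaves the response call to the site's principal investigator, and section 8.1.8 states that the study is open-label. Section 9.2.1 and the synopsis place the CR rate at 12 months. Sections 5.2 and 11.7 analyse lesions with CR as best overall response, which Appendix 5 runs to the 24-month visit.

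**The concern.** Consider one lesion: something is still visible at 12 months, it is biopsied as section 9.1.3 requires, and the result is negative. The fifth bullet makes it not CR, because visual CR is missing. The sixth bullet names visible tumour as a case where histology separates partial response (PR) from CR, so a negative result can make it CR.

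This is not a remote case, because visibility is one of the stated reasons for taking the biopsy. Two sites that both follow the protocol can classify the same lesion differently. One site can also choose between the bullets after seeing the biopsy result, with no blinding and no second reader named. The quantity affected is the primary endpoint, where only a handful of non-CR lesions can be tolerated.

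**Working it through.** **Step 1: can the two bullets be reconciled?**

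| Visual status at 12 months | Biopsy | Fifth bullet | Sixth bullet |
|---|---|---|---|
| Not visible | Negative | CR | CR |
| Not visible | Positive | Not CR | Not CR |
| Visible | Positive | Not CR | Not CR |
| Visible | Negative | **Not CR** | **CR allowed** |

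One might read the sixth bullet as letting histology only downgrade a visual CR. That fails, because the bullet expressly covers visible tumour, where there is no visual CR to downgrade. The fourth row stays in conflict.

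**Step 2: reproduce the plan's power statement.** Inputs from section 11.1 and Table 3: n = 120, one lesion per subject, one-sided alpha 0.025, and six pairs of threshold p0 and assumed CR rate p1.

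- Critical count r: the smallest r with P(X ≥ r | 120, p0) ≤ 0.025. Requiring the exact 95% lower limit to exceed p0 gives the same r.
- Power: P(X ≥ r | 120, p1).

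All six rows reach at least 80%, as the protocol states. Actual alpha is 0.016 to 0.022.

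**Step 3: sensitivity to the conflict.** The documents do not say how many lesions will be visible but biopsy-negative. Assume a share k of all lesions, with no visual CR at another visit, and assume that p1 counts them as CR. If they are not counted, power becomes P(X ≥ r | 120, p1 − k).

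| p0 / p1 | r | Non-CR allowed (120 − r) | Power, k = 0 | k = 1 pt | 2 pts | 3 pts | 5 pts |
|---|---|---|---|---|---|---|---|
| 85% / 94% | 110 | 10 | 89.3% | 78.1% | 63.5% | 47.9% | 22.0% |
| 86% / 94% | 111 | 9 | 81.6% | 66.9% | 50.6% | 35.3% | 13.8% |
| 87% / 95% | 112 | 8 | 85.3% | 70.6% | 53.5% | 37.1% | 14.1% |
| 88% / 96% | 113 | 7 | 89.1% | 74.8% | 56.8% | 39.2% | 14.4% |
| 89% / 97% | 114 | 6 | 93.0% | 79.4% | 60.6% | 41.5% | 14.7% |
| 90% / 97% | 115 | 5 | 84.7% | 65.2% | 44.2% | 26.8% | 7.5% |

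One point is about 1.2 lesions (0.01 × 120), and it takes every row below 80%.

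**Step 4: when the true rate is higher.** Section 11.1 expects a CR rate close to 100%. Take a shift of six lesions (0.05 × 120):

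- From 119 CRs: 119 − 6 = 113, exact lower limit 88.35%. This still passes 88% but no longer 89% or 90%.
- From 116 CRs: 116 − 6 = 110, exact lower limit 85.21%. This still passes 85% but no higher row, whereas 116 passes all six.

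Whether the conclusion changes therefore depends on the starting count and the threshold.

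**The case against.** The best defence is that the sixth bullet is permissive, directly follows the statement that histology alone cannot decide response, and never says outright that a negative biopsy upgrades a visible lesion. That narrows the conflict but does not remove it. The bullet still names visible tumour as a case for separating PR from CR, and nothing says which bullet prevails.

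Four further objections limit the point, and they stand:

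- A reader might infer that the note under Table 4 also lets a biopsy turn a visible residual into CR. It does not go that far. It covers tissue that is hard to distinguish from normal, where the visual call is uncertain, and it fits the fifth bullet. It simply does not settle the clearly visible case.
- A reader might infer that recurrence after CR is left without any rule at 24 months. Table 4 makes CR at 12 months with a new lesion at the treated site PD at 24 months. What is unstated is narrower: how a positive 24-month biopsy, as such, is classified at that visit.
- Under best overall response, a lesion with visual CR at 6 or 24 months may count as CR whichever bullet is followed.
- Not every biopsied lesion is a doubtful one, since routine site practice is also a trigger.

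It could also be said that this belongs in the statistical analysis plan. The sensitivity analysis does. The classification does not: sites assign it from Appendix 5, and a later analysis cannot undo it unless visual status and biopsy result are recorded separately.

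**Conclusion.** The point holds in limited form. Appendix 5 contradicts itself on one case, the lesion visible at 12 months with negative histology, and the protocol sends that case to biopsy. It affects the 12-month CR rate directly, and the best-overall-response analysis only through lesions with no visual CR at another visit.

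The size is conditional. The power losses above rest on an assumed share of 1 to 5 points, on one lesion per subject, on n = 120 (a stated minimum from about 210 recruited), and on planned CR rates that count these lesions as CR. With a true rate near 100% the conclusion may not change. It would go too far to say that the conflict will make the trial fail. A drop from 113 to 107 of 120, for example, starts at the lowest count that passes 88%, and the documents do not support treating that as the expected case.

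It would also go too far to say that a positive 24-month biopsy must cancel an earlier CR. Under best overall response that either has no effect or replaces the primary endpoint with a different one.

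**What to change.** - Replace the fifth and sixth bullets with one lesion-level rule that says explicitly whether a visible, biopsy-negative lesion is CR. Set it before response is assessed and apply it at both visits with scheduled histology, 12 and 24 months. No histology rule is needed for 6 months.
- Record visual status and histology result as separate items in the eCRF, so that either classification can be derived.
- Report the primary CR rate under the chosen rule, with the other classification as a named sensitivity analysis.
- State how a positive 24-month biopsy is classified at that visit under Table 4, leaving the best-overall-response endpoint as it is.

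The cost is a short change to Appendix 5, separate data fields if the eCRF lacks them, and one additional analysis. No extra biopsies are needed. If the stricter rule is chosen, the reported CR rate may be slightly lower.

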#### Response review

- Response is determined by the site PI

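### Appendix 5 gives conflicting guidance on whether a lesion still visible at 12 months with a negative biopsy is a complete response

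*Protocol*

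**What the plan says.** Four places in Protocol Appendix 5 bear on a lesion that can still be seen at 12 months and has been biopsied with a negative result.

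- Methods of Measurement, histology bullet: "Tumour histology alone cannot be used to assess response". If a 12-month biopsy is taken, "this histology must be negative in addition to CR visually, for a patient to be considered in complete response".
- Methods of Measurement, the bullet directly after it: "Histology can be used to differentiate between PR and CR at the 12-month mark if tumour is visible, suspected or is site clinical practice".
- Evaluation of target lesions: "Complete Response (CR): Disappearance of all target lesions", with no exception for histology.
- The note below Table 4, for residual tissue that is hard to tell from normal skin: "it is recommended that the residual lesion be investigated (biopsy/Histology) to confirm the complete response status".

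Section 9.1.3 says when the biopsy is taken at the 12-month visit: "Histology to be performed if lesion is visible, suspected or if this is the site's regular clinical practice". The 24-month visit carries essentially the same instruction. On who decides, Appendix 5 (Response review) says: "Response is determined by the site PI".

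The endpoint is used in two ways. Section 9.2.1 and the Synopsis evaluation criteria call for a CR rate at 12 months. Section 11.7 counts a lesion as CR if CR is its best overall response, and Appendix 5 takes best overall response from treatment to the 24-month visit.

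**The concern.** The two neighbouring bullets cover the same finding and point in different directions. If visual clearance is a necessary condition, histology has nothing to separate when tumour is visible: that lesion is PR or worse whatever the biopsy shows. The second bullet has content for visible lesions only if a negative biopsy can move them to CR.

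The protocol's own instructions produce this case, because a visible lesion is a stated trigger for biopsy. Seven sites take part and no reviewer other than the site PI is named. Two investigators who both follow the text could record PR and CR for the same finding. The matter also cannot safely wait for the analysis stage: unless the eCRF keeps this finding apart, the analyst cannot later recover which rule a site used.

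**Working it through.** **Step 1. The passages side by side.** The case is a lesion visible at 12 months with a negative biopsy.

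| Place in Appendix 5 | Result for this case | Stated or implied |
|---|---|---|
| Methods of Measurement, first histology bullet | Not CR | Follows directly: visual CR is required as well |
| Evaluation of target lesions | Not CR | Follows if the visible finding is the lesion |
| Methods of Measurement, second histology bullet | CR possible | Implied by permissive wording |
| Note below Table 4 | CR possible | Implied: biopsy is there to confirm CR |

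No sentence ranks one above another.

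**Step 2. Reproduce the plan's own figure.** Section 11.1 states that 120 subjects, one lesion each, give at least 80% power at one-sided alpha 0.025 for each row of Table 3. With an exact binomial test:

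- pass mark r = smallest r with P(X ≥ r | n = 120, p0) ≤ 0.025
- power = P(X ≥ r | n = 120, p1)

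| Threshold p0 | Assumed CR p1 | r | Power |
|---|---|---|---|
| 85% | 94% | 110 | 89.3% |
| 86% | 94% | 111 | 81.6% |
| 87% | 95% | 112 | 85.3% |
| 88% | 96% | 113 | 89.1% |
| 89% | 97% | 114 | 93.0% |
| 90% | 97% | 115 | 84.7% |

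The stated power holds in every row, so the sample size is not at issue.

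**Step 3. One lesion near the boundary.** Take the 87% row. The exact lower 95% limit for x CRs is the p that solves P(X ≥ x | 120, p) = 0.025.

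- x = 112 (112/120 = 93.3%): lower limit 87.3%, clears 87%.
- x = 111 (111/120 = 92.5%): lower limit 86.2%, does not.

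**Step 4. Illustration of a strict rule.** The share of visible, biopsy-negative lesions is not in the documents, so 2% to 5% is assumed. Start from a 97% CR rate that counts these lesions as CR, and move every one of them to non-CR:

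| Share moved | CR rate left | Chance of 112 or more of 120 |
|---|---|---|
| 0% | 97% | 99.0% |
| 2% | 95% | 85.3% |
| 3% | 94% | 70.6% |
| 5% | 92% | 37.1% |

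The number 120 is the stated minimum for analysis. The protocol asks for 25 subjects at each of 7 sites, 25 × 7 = 175. At n = 175 the same test at 87% needs 162 CRs, and the chance of passing is 94%, 83% and 46% for CR rates of 95%, 94% and 92%. The loss is smaller, but present.

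**Step 5. Which rate is exposed.**

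- The 12-month CR rate takes the full effect.
- For CR as best overall response, a lesion scored CR at 6 or 24 months counts whatever was recorded at 12 months. Only lesions without a CR at either visit are exposed, so Step 4 is an upper illustration for that endpoint.

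**The case against.** The best case for the protocol is that the passages can be read together. CR means that the lesion has gone, not that the skin looks untouched. The note below Table 4 is limited to tissue that is hard to tell from normal skin. If a biopsy shows that such tissue is not disease, the investigator can call the lesion gone, and the first bullet is met as well. Induration and pigment change are graded separately as treatment effects under Appendix 1, and nothing tells sites to score them as residual lesion. This reading fits the note. It does not explain the second bullet, which speaks of tumour being visible and not of doubtful tissue. The conflict narrows but remains.

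It is also fair that the lenient outcome is never stated. A reader might infer that the protocol sets out two flatly opposite rules; the second bullet is permissive and names no result for a negative biopsy, so the documents support an implied conflict only.

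A reader might also take the fall from 99% to between 85% and 37% as the expected damage to the primary analysis. The documents do not support that either. The figures rest on an assumed share, the minimum sample size, one lesion per subject, and every affected lesion becoming non-CR at all sites. They ignore best overall response, and they show what a strict rule would cost, not what the present ambiguity costs.

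**Conclusion.** The concern holds as a conflict in guidance. For a lesion visible at 12 months with a negative biopsy, Appendix 5 supports both not CR and CR, does not say which applies, and leaves the decision to the site PI. The 12-month CR rate is directly exposed. The primary best-overall-response CR is exposed only through lesions not scored CR at 6 or 24 months.

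The size is unknown, because the frequency of such lesions is not given. What can be said without assuming a frequency is that, at 120 subjects with one lesion each and an 87% threshold, one lesion classified differently can change the conclusion near the boundary. The 2% to 5% range serves only to show sensitivity.

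**What to change.** Reconcile the two histology bullets in Methods of Measurement with the CR definition under Evaluation of target lesions and with the note below Table 4. State one classification rule, applied at all sites and at every visit where histology is taken.

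Record *visible residual, histology negative* as its own eCRF category. Report the CR rate under the other reading as a prespecified sensitivity analysis.

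Either rule would end the ambiguity. Requiring visual disappearance, plus negative histology when it was taken, is the conservative option for the primary analysis. Its price is a lower stated CR rate and lower power, by an amount that depends on how common the finding is.

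The change itself costs some appendix wording, one eCRF category and one extra analysis. It needs no added biopsies and does not alter treatment.

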#### Baseline documentation of Target lesions

- All measurable lesions up to a maximum of three lesions should be identified as **target lesions** and recorded and measured at baseline.
- Target lesions should be selected on the basis of their size (lesions with the longest diameter) and their suitability for accurate repeated measurements (either by imaging techniques or clinically). In addition, the lesions and subject should meet the inclusion criteria.
- A sum of the longest diameter (LD) for *all target lesions* will be calculated and reported as the baseline sum LD. The baseline sum LD will be used as reference by which to characterize the objective tumour.

### Response Criteria

#### Evaluation of target lesions

- \* Complete Response (CR): Disappearance of all target lesions
- \* Partial Response (PR): At least a 30% decrease in the sum of the LD of target lesions, taking as reference the baseline sum LD
- \* Progressive Disease (PD): At least a 20% increase in the sum of the LD of target lesions, taking as reference the smallest sum LD recorded since the treatment started or the appearance of one or more new lesions
- \* Stable Disease (SD): Neither sufficient shrinkage to qualify for PR nor sufficient increase to qualify for PD, taking as reference the smallest sum LD since the treatment started

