**Primary endpoint:**

- The number and percentage of lesions achieving CR during the study

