**Efficacy:**

1. Rate of complete response (CR) for subjects treated with Rhenium-SCT at 12 months after treatment

MODIFIED VISUAL RECIST (adapted from Response Evaluation Criteria in Solid Tumours) CRITERIA 1.1

- Complete response (CR): disappearance of the target lesion/s
  - Partial Response (PR):  $\geq 30\%$  reduction of the larger initial diameter of the target lesion or sum of the larger initial diameters of the target lesions
  - Progressive Disease (PD):  $\geq 20\%$  increase in the largest initial diameter of the lesion or sum of the larger initial diameters of the target lesions
  - Stable Disease (SD): Neither partial response or progressive disease
2. Quality of Life (Baseline: prior to therapy, 6 months after therapy, and 12 months after therapy) – NMSC QOL questionnaire
  3. Overall response rate (ORR)
  4. Comfort of treatment with Rhenium-SCT using short questionnaire
  5. Cosmetic outcome (measured 12 months after therapy) using VAS. Both subject and clinician assessed.

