## 9.2 Efficacy Assessments

### 9.2.1 Response Assessments

The rate of Complete Response (CR) for subjects treated with Rhenium-SCT will be calculated at 12 months post-therapy.

An interim analysis is planned once 50% of the subjects have had their 6-month Follow-Up visit.

Treatment responses will be assessed according to the MODIFIED VISUAL RECIST at Baseline and during the Treatment and Follow-Up phases. If an assessment during the study results in Progressive Disease (PD) according to MODIFIED VISUAL RECIST, subjects will be withdrawn and further treated off study.

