## 11. STATISTICAL METHODS

### 11.1 Determination of Sample Size

The primary objective of the study is to estimate CR rate and show non-inferiority to historical values for CR rate following surgery and or radiotherapy. Complete response rate for BCC is 91% at 5 years and for SCC 79%. Review of the published papers for brachytherapy shows the split between BCC and SCC is 2:1, 1.68:1 and 2.1:1.

Based on previous studies, the CR rate for BCC and SCC is expected to be close to 100% following Rhenium-188 SCT treatment. For simplicity, assuming 1 lesion per subject, a sample size of 120 subjects is sufficient to provide at least 80% power to conclude non-inferiority using a one-sided alpha of 0.025 under the following circumstances (Table 3).

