**Table 3. Sample size calculation**

| Non-inferiority margin | Assumed CR rate |
|------------------------|-----------------|
| 85%                    | ≥94%            |
| 86%                    | ≥94%            |
| 87%                    | ≥95%            |
| 88%                    | ≥96%            |
| 89%                    | ≥97%            |
| 90%                    | ≥97%            |

CR: complete response

Note. A series of simulations (1000) were run to explore the potential impact of different ratios of BCC:SCC on the estimated overall, historical CR rate, assuming the SCC rate was 79% and the BCC rate 91%.

For ratios between 1.5:1 (BCC: SCC) to 3.5:1, the range of median (from simulation) overall CR rate was 87% to 89%. Accordingly, the table above is applicable irrespective of the BCC:SCC ratio.

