## **11.7 Efficacy Analyses**

### **Primary efficacy endpoint: Complete Remission (CR)**

The number of lesions treated per subject will be summarised.

The number (and percentage) of lesions in each category (CR, partial response [PR], stable disease [SD] and progressive disease [PD]) at each timepoint, and the overall best response will be presented. The percentage of lesions achieving CR during the study (i.e., CR is the

best overall response) will be estimated and presented with exact 95% confidence limits overall and by tumour type.

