**Table 5. Example Modified Visual RECIST data collection:**

|                      | Location        | Baseline   | Follow up 6 months | Follow up 12 months | Follow up 24 months |
|----------------------|-----------------|------------|--------------------|---------------------|---------------------|
|                      |                 | Dimensions | Dimensions         | Dimensions          |                     |
| Target lesion 1      | inner right ear | 2.3x2.1    | 1.8x1.5            | 1.6x1.3             |                     |
| target lesion 2      | outer right ear | 2.4x1.2    | 2.0x0.9            | 1.5x0.7             |                     |
| Target lesion 3      |                 |            |                    |                     |                     |
| Sum Longest Diameter |                 | 4.7        | 3.8                | 3.1                 |                     |
| Response Rate %      |                 | N/A        | 19.1               | 34                  |                     |
| Response Category    |                 |            | Stable Disease     | Partial Response    |                     |

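### The primary endpoint counts lesions, but Appendix 5 rates response for the subject, so the response rules do not yield the lesion categories that section 11.7 requires

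*Protocol*

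**What the plan says.** **Lesion as the unit.** The synopsis gives the primary endpoint as "The number and percentage of lesions achieving CR during the study". Sections 5.1 and 5.2 agree. Section 11.7 and its synopsis counterpart ask for "The number (and percentage) of lesions in each category" (CR, PR, SD, PD) at each timepoint, then the percentage of lesions with CR as best response, with an exact 95% interval.

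**Subject as the unit.** Appendix 5 holds the detailed rules.
- CR is "Complete Response (CR): Disappearance of all target lesions". PR, SD and PD use the summed longest diameter of the target lesions.
- The 12-month histology condition is stated for a patient.
- Table 5 lists dimensions for each lesion, but has one "Sum Longest Diameter" row and one response category per visit.
- Section 9.2.1 says "The rate of Complete Response (CR) for subjects treated with Rhenium-SCT will be calculated at 12 months post-therapy". The synopsis efficacy criteria say "Rate of complete response (CR) for subjects treated with Rhenium-SCT at 12 months after treatment".

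**Mixed wording.** The category definitions under the synopsis efficacy criteria cover both one lesion and the sum of several.

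**Sizing.** Section 11.1 states that "a sample size of 120 subjects is sufficient to provide at least 80% power to conclude non-inferiority using a one-sided alpha of 0.025", assuming one lesion per subject. Section 7.1 allows up to three target lesions for evaluation.

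**The concern.** With one target lesion the two units coincide. With two or three they do not. A lesion that has gone is a CR under section 5.2, but its subject is not in CR under Appendix 5 if another target lesion remains. No passage says how a single lesion gets its category, so Appendix 5 applied as written cannot fill the table that section 11.7 requires.

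The stated aim in section 11.1 is to compare the CR rate with a historical value. Two CR rates on different units, both supported by the text, leave room to choose between them once the data are known. The study is open-label and the site investigator determines response.

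**Working it through.** **1. The plan's own figure.** Inputs: n = 120, one-sided alpha 0.025 and the six Table 3 pairs. The pass mark r is the smallest count with P(X ≥ r | 120, bound) ≤ 0.025. Power is P(X ≥ r | 120, assumed rate).

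| Bound | Assumed CR | r | Power |
|---|---|---|---|
| 85% | 94% | 110 | 89.3% |
| 86% | 94% | 111 | 81.6% |
| 87% | 95% | 112 | 85.3% |
| 88% | 96% | 113 | 89.1% |
| 89% | 97% | 114 | 93.0% |
| 90% | 97% | 115 | 84.7% |

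All rows reach 80%, so the sizing reproduces for one lesion per subject.

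**2. What Table 5 rates.** The sums are 2.3 + 2.4 = 4.7, then 3.8, then 3.1. (4.7 − 3.8)/4.7 = 19.1% and (4.7 − 3.1)/4.7 = 34.0%, as printed. The single lesions give 21.7% and 16.7% at 6 months, and 30.4% and 37.5% at 12 months. The printed percentages therefore come from the sum. In this example each lesion would fall in the same category as the sum, so the example does not show the conflict.

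**3. Subject CR implied by a lesion CR rate p.** The lesion mix and the within-subject correlation are not in the protocol, so these are assumptions. With independent lesions, subject CR = w1·p + w2·p² + w3·p³, where w1, w2 and w3 are the shares of subjects with 1, 2 and 3 lesions.

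At p = 0.95, p² = 0.9025 and p³ = 0.857. For a 70/20/10% mix: 0.7 × 0.95 + 0.2 × 0.9025 + 0.1 × 0.857 = 0.931.

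Chance of at least 112 of 120 (the 87% bound), for a test on subjects:

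| Mix, 1/2/3 lesions | Lesion CR | Subject CR | Chance of passing |
|---|---|---|---|
| All one lesion | 95% | 95.0% | 85% |
| 80/15/5% | 95% | 93.8% | 68% |
| 70/20/10% | 95% | 93.1% | 56% |
| 60/25/15% | 95% | 92.4% | 44% |
| 70/20/10% | 98% | 97.2% | 99% |

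Correlation narrows the gap. For 70/20/10% at 95% lesion CR and an intraclass correlation of 0.5, subject CR is 94.1% and the chance is about 73%.

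**4. One data set, two answers (assumed).** Take 120 subjects, of whom 96, 18 and 6 have 1, 2 and 3 lesions: 96 + 36 + 18 = 150 lesions. Nine lesions fail, in nine different subjects.
- By lesion: 141/150 = 94.0%, exact lower limit 88.9%.
- By subject: 111/120 = 92.5%, exact lower limit 86.2%.

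At a bound of 87% or 88% the lesion rate passes and the subject rate fails. At 85% and 86% both pass, and at 89% and 90% both fail. Part of the difference in lower limits comes from the larger lesion denominator, which the exact interval treats as independent.

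If the nine failures sit in three subjects with three lesions each, subject CR is 117/120 = 97.5%. That is above the lesion rate, so the gap can go either way.

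**The case against.** The strongest reply is that the primary unit is not in doubt. Objective, endpoint and analysis all say lesions, and neither 9.2.1 nor the synopsis criterion calls its subject rate primary. Words such as subjects treated may simply name the population. Lesion CR can be derived from dimensions already planned for each lesion, and an analysis plan could do so. Much of this stands: the data needed are collected. What remains is that such a derivation would depart from the protocol's own CR definition and from its patient-level histology rule, and neither should be settled outside the protocol.

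Four stronger readings are tempting, and the documents do not support them.
- **That every response definition is per subject.** The synopsis definitions also allow a single-lesion reading.
- **That sites will record only a subject category and copy it to each lesion.** Table 5 is labelled an example, the eCRF is not shown, and no passage says that the category is carried over.
- **That the non-inferiority result will change.** Section 11.7 plans no subject-level test, the lesion mix is assumed, no single bound is fixed, and section 11.1 expects CR close to 100%.
- **That a sum can hide a growing lesion and so distort the primary result.** If one lesion goes from 20 to 0 mm and another from 8 to 12 mm, the sum falls from 28 to 12 mm (−57%, PR) although the second lesion grew by 50%. That second lesion is non-CR either way. Only the descriptive PR and PD counts, and the rule on leaving the study for PD, are touched.

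**Conclusion.** The contradiction is in the current text and goes beyond missing detail. For subjects with two or three target lesions, the Appendix 5 rule gives a different CR status from the one that the primary endpoint needs.

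Its numerical effect is conditional. It is zero with one lesion per subject. With 95% lesion CR, an 87% bound, independent lesions and the assumed mixes, the chance of passing falls from 85% to between 44% and 68% if subjects rather than lesions are tested. At 98% lesion CR with the 70/20/10% mix it is about 99%. A changed conclusion is therefore possible at the lower Table 3 rates and unlikely near the rate that the sponsor expects. The reason to correct it is that the primary endpoint should have one definition, whatever the rate turns out to be.

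**What to change.** 1. State in the synopsis efficacy criteria, 5.2, 9.2.1 and Appendix 5 that the primary CR is rated per lesion, on that lesion's own longest diameter, with CR meaning that this lesion has gone. Apply the 12-month histology condition to the lesion sampled.
2. Define PR, SD and PD for the section 11.7 lesion table on the same unit. Add a category per lesion and visit to Table 5 and to the eCRF.
3. Report all target lesions in CR, and the sum-of-diameters categories, as a named supportive subject-level result.
4. Sections 9.1.4 and 9.2.1 make subjects leave the study for PD. The sponsor must reconcile these passages with the response definitions so that the unit of that PD is stated and the withdrawal rule is not altered by default.

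The cost is amendment wording and one derived field per lesion and visit. Table 5 already provides for lesion dimensions, so no extra visits or patients are needed.
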